### Objectives

*Primary objective:* to establish if the addition of dexamethasone to treat patients presenting to urgent secondary care with cellulitis reduces total pain reported over the first 3 days (postrandomisation) compared with a control (placebo).

*Secondary objectives:* to determine whether the addition of dexamethasone, when compared with a control (placebo), to treat patients with cellulitis presenting to urgent secondary care with cellulitis: (a) improves quality of life and other patient-reported outcomes, (b) reduces subsequent antimicrobial prescribing, analgesia usage and healthcare utilisation and (c) is cost-effective.

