#### Secondary outcomes

For the secondary outcomes, listed below, continuous outcomes will be reported as means and binary/categorical outcomes will be reported as percentages at the specified timepoints.

Health-related quality of life, measured by EuroQol 5 Dimension 5 Level (EQ-5D-5L)^20^ at day 3, day 14 and day 90 postrandomisation.Patient Global Impression of Improvement (PGI-I)^21^ measured daily for first 3 days (via SMS at T2, T4 and T6) and at day 14 postrandomisation.Analgesia usage (number and type of analgesia taken over first 3 days) postrandomisation, collected at day 14.Antibiotic usage (route, type and postrandomisation length of course) up to day 14 postrandomisation.(Re)admissions to hospital by day 14 postrandomisation.Complications of dexamethasone use by day 14 postrandomisation.Unscheduled healthcare usage until day 14 postrandomisation.Health, social care and broader societal resource use, measured by a resource use questionnaire based on the Modular Resource Use core module (ModRUM)^22^ tailored to the study population, to day 90 postrandomisation.Recurrence of cellulitis by day 90 postrandomisation.Serious and/or potentially related adverse events by day 90 postrandomisation.Pain experienced at day 14 postrandomisation, measured using NRS^23^ (0–10).

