Secondary continuous outcomes (PGI-I, pain at 14 days) will be analysed using mixed-effects linear regression models if assumptions are met; PGI-I at days 1, 2 and 3 will use a mixed-effects repeated measures model. Alternative modelling (eg, mixed-effects ordinal logistic models, dichotomisation for logistic regression) will be considered if assumptions are not met, detailed in SAP. Dichotomous secondary outcomes (additional antibiotic use, (re)admission, unscheduled healthcare use, recurrence) will be analysed using mixed-effects logistic models (if event numbers allow). All models will adjust for the same factors as the primary analysis. Adjusted differences in means or ORs (with 95% CIs) will be reported, along with unadjusted estimates.

Descriptive analysis will cover compliance, analgesia details, antibiotic details and dexamethasone-related complications. The estimands framework for secondary outcomes will mirror the primary outcome. Multiple imputation may be considered for missing secondary outcome data. SAEs will be reported descriptively by whether the first dose was taken (not intention to treat (ITT)).

Exploratory subgroup analyses on the primary outcome (not powered for) will be pre-specified for: cellulitis location (lower limb vs other) and NSAID usage at randomisation (user vs non-user). The primary analysis model will be refitted including an interaction term between treatment and the subgroup of interest; minimum numbers for these analyses will be pre-specified in the SAP.

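### Reducing analgesia usage is a secondary objective, but the stated analysis of analgesia is descriptive only, with no between-arm estimate or 95% CI

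*Protocol article*

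**What the plan says.** All of this is in the protocol article.

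- **Objectives.** The secondary objectives are comparative, dexamethasone against placebo. Part (b) asks whether the drug "reduces subsequent antimicrobial prescribing, analgesia usage and healthcare utilisation".
- **Secondary outcomes.** One listed outcome is "Analgesia usage (number and type of analgesia taken over first 3 days) postrandomisation, collected at day 14".
- **Statistical methods, modelled outcomes.** For continuous measures: "Secondary continuous outcomes (PGI-I, pain at 14 days) will be analysed using mixed-effects linear regression models if assumptions are met". For binary ones: "Dichotomous secondary outcomes (additional antibiotic use, (re)admission, unscheduled healthcare use, recurrence) will be analysed using mixed-effects logistic models", provided there are enough events. These models carry the covariates of the primary analysis, and adjusted and unadjusted estimates are promised, the adjusted ones with 95% CIs.
- **Statistical methods, descriptive outcomes.** "Descriptive analysis will cover compliance, analgesia details, antibiotic details and dexamethasone-related complications".

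The same section says that the estimands for secondary outcomes follow the primary one, and that the emphasis is on estimation over testing.

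**The concern.** An objective that asks whether a treatment reduces something calls for a between-arm contrast and a statement of its uncertainty. Here the objective is comparative, the outcome is defined and the data are collected, but the analysis assigned to it is description. Analgesia is also the only one of the three components of objective (b) treated this way.

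Analgesia also bears on how the main result is explained. It is part of usual care in both arms, and the primary estimand takes pain scores whatever analgesia was used (treatment policy). If placebo participants took more analgesia, some of the benefit of dexamethasone would appear as lower analgesic use and not as a larger pain difference. An analgesia estimate over the same 3 days would help a reader judge that. The article gives no analgesia rates, so whether such a difference will arise is unknown.

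**Working it through.** **1. Match each part of objective (b) to its stated analysis.**

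| Part of objective (b) | Stated analysis | Estimate and 95% CI stated? |
|---|---|---|
| Antimicrobial prescribing | Mixed-effects logistic model for additional antibiotic use; further antibiotic details described | Yes |
| Healthcare utilisation | Mixed-effects logistic models for (re)admission and unscheduled use | Yes |
| Analgesia usage | Described | No |

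Antibiotics also appear in the descriptive list, but they have a modelled counterpart. Analgesia has none. Nor is this silence that an unseen SAP might fill: the article expressly places analgesia under description.

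**2. Confirm that the sample size is not in question.** Inputs from the Sample size section: difference 10, SD 30, two-sided 5%, 90% power, 15% loss.

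- Normal approximation: n = 2 × (1.960 + 1.282)² × (30/10)² = 2 × 10.51 × 9 ≈ 189.1, so 190 per group.
- The t-test solution is 190.1, which rounds up to the stated 191.
- Allowance for loss: 191 / 0.85 = 224.7, so 225 per group and 450 in total, as stated.

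**3. Ask what precision an analgesia contrast would have.** The article gives no analgesia rate, so the proportion p using a chosen class of analgesic is assumed to lie between 30% and 70%. The unadjusted 95% half-width for a risk difference is 1.96 × √(2p(1−p)/n).

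| n per arm | p = 30% or 70% | p = 50% |
|---|---|---|
| 191 | 1.96 × √(0.42/191) = 9.2 points | 1.96 × √(0.50/191) = 10.0 points |
| 225 | 1.96 × √(0.42/225) = 8.5 points | 1.96 × √(0.50/225) = 9.2 points |

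The planned logistic model reports odds ratios, so the same precision is worth giving on that scale. The standard error of the log odds ratio with equal proportions is √(2/(n·p(1−p))). For n = 191:

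- p = 50%: √(2/47.75) = 0.205, and 1.96 × 0.205 = 0.401. Around an odds ratio of 1 the interval is about 0.67 to 1.49.
- p = 30% or 70%: √(2/40.11) = 0.223, and 1.96 × 0.223 = 0.438. The interval is about 0.65 to 1.55.

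These figures ignore covariates and site. The 191 is the number expected to have primary pain data; the number with analgesia data at day 14 is not stated and may differ.

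**The case against.** The strongest reply is that description is a reasonable choice. The outcome is a number and a type of analgesic, gathered at day 14 about the first 3 days, so it has many categories and rests partly on recall, although participants are offered a diary. The Secondary outcomes section also says that "continuous outcomes will be reported as means and binary/categorical outcomes will be reported as percentages at the specified timepoints". If those summaries are given by arm, as is natural in a randomised trial, a reader can work out a crude difference and interval. This stands in part. It means that the objective is not left without information, and a reader who inferred that it cannot be answered, or that no estimate could be had, would go too far. What is missing is a pre-specified, adjusted between-arm estimate with its interval, of the kind promised for the rest of objective (b). Recall is a reason for caution in interpreting the result, or for softening the objective, but it does not reconcile the two statements.

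A reader might also infer that a small or null pain difference would be uninterpretable without an analgesia model. The article does not support that. Its estimand compares dexamethasone plus usual care with placebo plus usual care, and usual care includes analgesia. The pain difference stands on its own as the net effect; an analgesia estimate would help explain it.

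Finally, a reader might extend the point to quality of life, because EQ-5D-5L is a secondary outcome "at day 3, day 14 and day 90 postrandomisation" and is not among the named continuous models. That extension is not sustained. The Cost-effectiveness analysis section states an adjusted between-arm model for QALYs built on EQ-5D-5L at baseline, day 14 and day 90. A model for the score at each timepoint, including day 3, is something a condensed article may leave to the SAP or the health economics analysis plan, and nothing says that EQ-5D-5L will not be compared.

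**Conclusion.** The point holds for analgesia. The article states a comparative objective and then a descriptive analysis of the same outcome, while the companion parts of the objective are modelled with 95% CIs. The consequence is moderate: a secondary question would be reported without a pre-specified effect estimate, and neither the primary analysis nor the sample size changes.

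The planned trial could estimate a difference in a binary analgesia measure to within about 9 to 10 percentage points either way. That rests on about 191 participants per arm with analgesia data and on assumed use of 30% to 70%, neither of which the article supplies. The limitation is in the stated analysis, not in the data or the sample size.

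**What to change.** Move analgesia usage from the descriptive list to the modelled secondary outcomes. Pre-specify one binary measure, for example any use of a named class of analgesic in the first 3 days. Analyse it with the mixed-effects logistic model already planned and the same adjustment as the primary analysis, and report adjusted and unadjusted between-arm estimates with 95% CIs. Choose a class that is unlikely to be used by nearly everyone or nearly no one, or the comparison will say little. Keep the breakdown by number and type descriptive. If the trial team judges the day 14 data too weak for this, the alternative is to reword objective (b) so that it does not promise a comparison for analgesia. If the SAP already contains such a model, only the protocol wording needs to be aligned with it. Settle this before unblinding.

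The cost is a change of wording and a small amount of modelling on data already being collected. The downside is a few more secondary comparisons, on an outcome that depends partly on recall; both should be acknowledged when the result is reported.

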### Cost-effectiveness analysis

A full within-trial cost-effectiveness analysis (CEA) will be conducted from an NHS and Personal Social Services perspective to estimate the incremental cost-effectiveness of dexamethasone versus placebo. Resources and costs of providing oral dexamethasone will be established. Participant health, social care and broader societal resource use will be captured at baseline and day 90 using a self-report resource use questionnaire tailored for this population with patient advisory group (PAG) input. Nationally recognised UK health and social care unit costs will be applied. Quality-adjusted life-years (QALYs) will be estimated using EQ-5D-5L data collected at baseline, day 14 and day 90. The ‘cross-walk’ algorithm will map EQ-5D-5L to EQ-5D-3L UK general population valuation survey data, per National Institute for Health and Care Excellence (NICE) guidance. Descriptive statistics will summarise costs and QALYs by group. Mixed-effects linear regression models will test for differences in costs and QALYs, adjusting for age, sex, baseline pain, severity of cellulitis (Eron stage^27^ 1 vs all other stages), prior antimicrobial therapy for this episode prior to attending urgent secondary care, diabetes status (fixed effects) and recruitment site (random effect); cost models will also adjust for baseline costs and QALY models for baseline EQ-5D-5L values. ICERs will be presented for cost per total pain prevented (3 days) and cost per QALY (day 90). Sampling uncertainty will be accounted for, missing data explored for multiple imputation, and cost-effectiveness acceptability curves presented using the net-benefit approach against NICE thresholds (eg, £20 000–£30 000 per QALY). Broader societal perspectives will be considered in sensitivity analyses. A Health Economics Data Analysis Plan concordant with the trial SAP and Consolidated Health Economic Evaluation Reporting Standards (CHEERS)^28^ guidelines will be developed.

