### Intervention and comparator

#### Intervention

Participants in the intervention group will receive two 8 mg doses of oral dexamethasone. The first dose will be administered as soon as possible after randomisation, while in the urgent secondary care unit. The second dose is to be taken 24 hours later (±6 hours). If discharged, participants will take the second dose at home; if hospitalised, it will be administered by clinical or research staff. Each 8 mg dose consists of two 4 mg dexamethasone tablets overencapsulated into two separate capsules for blinding purposes. No modification of trial dosage is permitted in the study.

Dexamethasone was chosen for its high glucocorticoid activity and recent clinical experience in trials like RECOVERY.^17^ The dose (8 mg), route (oral) and course (two doses) were based on expert opinion suggesting additional benefit of a second dose at ~24 hours for pain outcomes. Given its half-life, the selected regimen is expected to affect swelling and pain over the subsequent 24–48 hours.

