### Outcomes

#### Primary outcome

Total pain experienced over the first 3 days postrandomisation.

Total pain will be calculated using the standardised area under the curve (AUC) approach from seven individual pain scores, measured using a 0–10 Numerical Rating Scale (NRS) (see wording in online supplemental file S2). The first (baseline) pain score is collected in person prerandomisation as part of a participant questionnaire pack. The remaining six scores are collected postrandomisation at approximately 12-hour intervals (around 8 am and 8 pm) via SMS survey (hereby referred to as timepoints 1–6 (T1–T6)). Actual time of response will be recorded. Alternative methods to collect pain scores (in-person, telephone) are available if SMS is not feasible, depending on staff capacity.

Total pain was chosen as the primary outcome after extensive Patient and Public Involvement (PPI) work. Reduction in erythema has previously been used as a cellulitis outcome measure by regulators,^18^ but was not chosen in this trial for multiple reasons. First, patient feedback was that pain and symptoms were much more important than the size of the erythema. Second, measurement of erythema might be biasing against those of skin of colour. Pain was identified as a key issue for patients with cellulitis, aligning with recent priority setting partnerships.^19^

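### The QALY calculation leaves out the day-3 EQ-5D-5L that the trial collects, so the cost-per-QALY result can understate an early, short-lived effect

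*Protocol article*

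**What the plan says.** The Secondary outcomes section lists EQ-5D-5L "at day 3, day 14 and day 90 postrandomisation". Table 2 adds a baseline measurement and places the day-3 one at T6, so four readings are scheduled. The Cost-effectiveness analysis section then names three of them: "Quality-adjusted life-years (QALYs) will be estimated using EQ-5D-5L data collected at baseline, day 14 and day 90". It gives no reason for dropping the fourth.

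The trial is built around the first days. The primary outcome is "Total pain experienced over the first 3 days postrandomisation", and the Intervention section says that "the selected regimen is expected to affect swelling and pain over the subsequent 24–48 hours".

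Two other statements bear on the point. The Secondary outcomes section reports continuous outcomes as means at each listed time, which includes EQ-5D-5L at day 3. The economic section plans two incremental ratios: one per unit of pain over 3 days and one per QALY at day 90. The NICE thresholds and the acceptability curves relate to the QALY result.

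**The concern.** QALYs are an area under the utility curve. With readings at baseline, day 14 and day 90 only, the first two weeks depend on the two ends of that interval. A utility difference that is present at day 3 and gone by day 14 contributes nothing, although the trial will have measured it. The same holds for an early harm, so the rule can err in either direction; for a drug that helps early, it understates the benefit.

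T6 is the only utility reading after randomisation that lies in or near the targeted period. T1 is sent at the first 8 am or 8 pm after randomisation and T6 follows 60 hours later, so T6 falls about 60 to 72 hours after randomisation. At stake are the incremental QALY, the cost per QALY and the acceptability curves. Cost-effectiveness is part of the stated research question, so these results matter even though they are secondary.

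**Working it through.** The article states no QALY figure, so there is none to reproduce. The check compares the three-point rule with a four-point rule.

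**Inputs from the article.** EQ-5D-5L times: 0, 3 (T6), 14 and 90 days. Times used for QALYs: 0, 14 and 90. Thresholds: £20 000 and £30 000 per QALY.

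**Assumptions, not stated in the article.** Trapezoidal area; no between-arm difference at baseline (the QALY model adjusts for baseline EQ-5D-5L) or at day 90; 365.25 days per year; illustrative d3 of 0.05, 0.10 and 0.15. The article gives no utility difference.

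**Formulas, in utility-days.**

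- Three-point plan: 14 × d14/2 + 76 × d14/2 = 7 × d14 + 38 × d14 = 45 × d14.
- Four-point version: 3 × d3/2 + 11 × (d3 + d14)/2 + 76 × d14/2 = 7 × d3 + 43.5 × d14.
- Shortfall of the plan: 7 × d3 − 1.5 × d14.

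**Share of the four-point 90-day gain that the plan misses.**

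| d14 as a fraction of d3 | Plan (× d3) | Four-point (× d3) | Missed |
|---|---|---|---|
| 0 | 0 | 7 | 100% |
| 0.10 | 4.5 | 11.35 | 60% |
| 0.25 | 11.25 | 17.875 | 37% |
| 0.50 | 22.5 | 28.75 | 22% |
| 1.00 | 45 | 50.5 | 11% |

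The share reaches one half where 45f = 7 − 1.5f, that is f = 7/46.5, about 0.15.

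**Size when d14 = 0** (shortfall 7 × d3/365.25).

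| d3 | QALY missed | At £20 000 | At £30 000 |
|---|---|---|---|
| 0.05 | 0.00096 | £19 | £29 |
| 0.10 | 0.00192 | £38 | £57 |
| 0.15 | 0.00287 | £57 | £86 |

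The absolute shortfall falls slowly as d14 rises. For d3 = 0.10 it is (0.70 − 0.075)/365.25 = 0.00171 QALY (£34 to £51) at d14 = 0.05, and (0.70 − 0.15)/365.25 = 0.00151 QALY (£30 to £45) at d14 = 0.10. The share falls faster because the plan's own gain grows.

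**Where the added area lies.** When d14 = 0, days 0 to 3 hold 1.5 × d3 and days 3 to 14 hold 5.5 × d3, which is 79% of the total. For d3 = 0.10, the part inside the first 3 days is 0.15/365.25 = 0.00041 QALY, about £8 at £20 000 per QALY and £12 at £30 000.

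**The case against.** The strongest objection concerns the replacement. Most of what day 3 adds is a straight line drawn from day 3 to day 14, not measured benefit. Suppose d14 = 0 and the true difference rises linearly to d3 at day 3, then falls linearly to zero at day t. The true area is 1.5 × d3 + (t − 3) × d3/2 = (t/2) × d3. The three-point rule records 0 and the four-point rule 7 × d3, so the four-point rule is closer only when t exceeds 7 days. An effect that fades soon after day 3 would be over-credited, and one already gone by T6 is missed by both rules. This stands as a reason to report both versions; for the pattern just described, they bracket the truth. It is not a reason to leave out the only early utility reading without comment.

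A reader might infer that most of the 90-day QALY gain is lost. Within days 0 to 3 the plan does miss at least 1 − 3/14 = 79% of the four-point area whenever d14 is no larger than d3. Over 90 days, however, the loss exceeds half only if d14 is below about 15% of d3. The documents do not show that the difference has gone by day 14. The Introduction cites a prednisolone trial with clinical cure at 10.0 versus 14.6 days; that course was longer, so the evidence is indirect, but it makes some day-14 difference plausible.

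A reader might also infer that day-3 EQ-5D-5L goes unused, or that the early window has no economic result. Neither is so: its mean is reported, and the pain ratio covers those 3 days. What remains is that neither enters the QALY result.

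Finally, a Health Economics Data Analysis Plan is still to be developed and could add day 3. That makes correction easy, but the article names the three times explicitly, so this is a stated choice and not a detail left to the later plan.

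**Conclusion.** The point holds as a should-fix matter for one secondary economic estimate. The plan's QALY definition omits a scheduled reading in or near the period that the treatment targets, without explanation, and can return zero for a benefit that has gone by day 14. Depending on how much of the day-3 difference persists to day 14, the plan misses from 11% (all of it) to 100% (none of it) of the four-point 90-day gain. In the worst case, d14 = 0, this is about 0.001 to 0.003 QALY, or £19 to £86 per participant, for an assumed d3 of 0.05 to 0.15.

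These sizes rest on the trapezoid, on no difference at baseline or day 90, and on assumed utility differences. A reader might go further and infer that the cost-effectiveness conclusion would change. The article gives neither an incremental cost nor a QALY variance, so that cannot be shown. The primary outcome, sample size, randomisation, blinding and safety reporting are not affected.

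**What to change.** State in the protocol and in the Health Economics Data Analysis Plan, before analysis, that QALYs are the area under the EQ-5D-5L utility curve at baseline, day 3 (T6), day 14 and day 90. Name the interpolation rule, and keep the three-point version as a prespecified sensitivity analysis so that dependence on the day-3 to day-14 line is visible.

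The cost is about one sentence in each document, with no new data collection. The small downsides are some extra missing data at day 3, for which the section already contemplates multiple imputation, and reliance on interpolation between day 3 and day 14. Settling this now avoids a choice of time points that could later look driven by the results.

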### Patient and public involvement

A PAG will advise on study processes throughout the trial and includes the PPI coapplicant, North Bristol NHS Trust infection PAG and three additional members who have relevant lived experience and have been identified to join the group specifically for DEXACELL. The PAG will be involved at every stage of the trial including but not limited to reviewing and inputting into patient-facing materials. Throughout the trial, advising on the participant pathway and any potential recruitment barriers, and coproducing the dissemination materials to be shared with participants and the public once the trial results are available.

The study team have also worked with people who inject drugs who commonly suffer from cellulitis, via the Bristol Drugs Project, and patients with skin of colour where cellulitis looks different. This has helped to design an inclusive trial to ensure our research is relevant to these important groups.

The coapplicant patient representative sits on the Trial Management Group (TMG) and two independent lay members sit on the Trial Steering Committee (TSC).

